Repeated large volume paracentesis allows only temporary mobilisation of ascites and relief of symptoms. Insertion of a tunnelated peritoneal catheter (PleurX) allows repeated intermittent fluid drainage at smaller volumes. The PleurX catheter may therefore have beneficial effect on the management of ascites and improve quality-of-life as well as nutrition.

Objectives

To evaluate the beneficial and harmful effects of the PleurX catheter compared with large volume paracentesis.

Interventions

PleurX catheter compared with large volume paracentesis. Both interventions (PleurX catheter and large volume paracentesis) will be combined with albumin and the antibiotic ciproxin 500 mg once daily. The treatment with ciproxin 500 mg once daily will continue until the end of the trial. The PleurX cathether is approved for permanent placement. After completion of the trial, patients may choose to keep the PleurX or to have it removed.

*PleurX catheter*: The PleurX catheter is a tunnelated peritoneal catheter, designed for permanent placement in the peritoneal cavity (see appendix 6, pictures of the equipment). The catheter is placed by a trained, specialised physician under sterile conditions and with access to x-ray transillumination. All investigators involved in the placement of the PleurX catheter are specialised hepatologists with extensive experience in the management and observation of patients with refractory ascites including experience in the use of the PleurX and large volume paracentesis through their clinical work.

The catheter is 50 cm in length and is placed in the peritoneal cavity (Appendix). A small incision (approximately 1.5 cm) allows the catheter access to the peritoneal cavity from where fluid can be drained. The catheter is placed in a 5 to 8 cm subcutaneous tunnel and penetrates the skin at another incision. Initially, the catheter is attached to the skin with two sutures. A special cuff on the catheter allows entrenchment of the catheter in the subcutaneous fat. After 7-10 days, the incisions are healed and the catheter is simply wrapped in a soft bandage on the abdominal skin.

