Collection of blood tests for standard biochemical analysis, measurement of weight and hand grip strength and calculation of BMI.

Visit 5 (Day 90)

Patients have been fasting overnight.

Outpatient visit including collection of information about control of ascites (amount of ascites assessed using abdominal ultrasound and number of paracenteses since the last visit), adverse events and quality of life.

Collection of blood tests for standard biochemical analysis, measurement of weight and hand grip strength and calculation of BMI.

Visit 6 (Day 120)

Outpatient visit including collection of information about control of ascites (amount of ascites assessed using abdominal ultrasound and number of paracenteses since the last visit), adverse events and quality of life.

Collection of blood tests for standard biochemical analysis, measurement of weight and hand grip strength and calculation of BMI.

Visit 7 (Day 150)

Outpatient visit including collection of information about control of ascites (amount of ascites assessed using abdominal ultrasound and number of paracenteses since the last visit), adverse events and quality of life.

Collection of blood tests for standard biochemical analysis, measurement of weight and hand grip strength and calculation of BMI.

Visit 8 (Day 180; final assessment in the trial)

Patients have been fasting overnight.

Outpatient visit including collection of information about control of ascites (amount of ascites assessed using abdominal ultrasound and number of paracenteses since the last visit), adverse events and quality of life.

Collection of blood tests for standard biochemical analysis, measurement of weight and hand grip strength and calculation of BMI. The PleuX tunnelated catheter is removed if the subject decides that he/she would like the PleurX catheter removed after the final visit.

Unscheduled/Intermediate Visits

If patients are admitted between scheduled visits information about adverse events will be collected.

Medical device and labelling

The medical device tested is the PleurX tunnelated catheter (Pleurx Peritoneal Catheter System): CareFusion Pleurx Catheter Systems: K1 13854. The PleurX peritoneal catheter and sub devices relevant for the drainage procedure are listed in appendix: “Peritoneal Catheter Mini Kit Instructions for use_en”. Following precautions will be made when handling the medical device:

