- The PleurX Tunnelated Peritoneal Catheter is approved for permanent placement and catheter implantation is regular clinical practice prior to initiation of this study. Consequently the registration of medical device handling will include noting device LOT number in patient’s medical record and in the corresponding CRF.
- All peritoneal catheters are labeled with following information:
  - Manufacturers name and address: CareFusion, [name].
  - Exact description of package content.
  - Package content is STERILE.
  - LOT number.
  - Expiring date.
  - For single use only.
  - Warnings:
    - Do not use if package is damaged. Consult instructions for use. Contains phthalates.

Monitoring Procedures

Independent monitoring of the trial for clinical protocol and compliance will be conducted periodically (i.e., at a minimum of three monthly intervals) by qualified staff from the the GCP unit in the Capital Region. The sponsor-investigator will permit direct access to the study monitors and appropriate regulatory authorities to the study data and to the corresponding source data and documents to verify the accuracy of these data.

Other treatments

Other treatments that are considered necessary for the subject will be given at the discretion of the investigator. Administration of all other treatments will be recorded on the accompanying Case Report Form.

Procedures in case of emergencies

The investigator will ensure that the necessary procedures and expertise to handle emergency situations that may arise during the study will be available.

Adverse Events

Adverse events (AEs) are defined as any event, sign or symptom occuring during the study whether the AE is considered to be related to the intervention or not. All adverse events must be recorded in the patient's Case Report Forms.

If an AE occurs more than 1 week after the removal of the PleurX catheter or more than 1 week after completion of Visit 8, and there is no apparent causal connection or relation to the Pleurx catheter, this shall not be deemed to be an AE.

The median survival for patients with cirrhosis and diuretic resistant ascites is six months and mortality is therefore expected amongst study participants. Consequently fatal events due to chronic liver failure will not be categorised as a SADE.

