Furthermore the listed parameters below occur regularly amongst patients with decompensated cirrhosis and ascites. They are thoroughly evaluated and afterwards categorized, by specialized hepatologists, as not being associated with carrying a permanent tunnelated peritoneal catheter. As a result this list of events will not be categorised at SAE but will be registered as AE:

- Hospitalisation du to large volume paracenthesis
- Alterations in type and dose of medicine
- Planned outpatient control visits due to other chronical diseases
- Hospitalisations due to chronic liver failure
- Hospitalisations due to alcohol intoxication
- Diagnosis of Hepatocellular carcinoma or other malignant diseases

Some side effects of ascites are obtained by letting the study participants answer the Quality of Life Questionnaire at every visit. Therefore these side effects will not also be listed as Adverse Events:

- Stomach pain or soreness
- Nausea
- Anorexia
- Reduced appetite
- Alterations in bowel habits
- Fatigue
- Dyspnoea
- Negative alterations in physical capability
- Leg pain

The type, potential relationship, severity, starts and end date for all AE must be recorded. The severity of the adverse event and the relationship with the study medical device must be assessed in accordance with the guidelines described below.

*The investigator must assess the relationship between an adverse event and the study medical device using the following guidelines:*

Adverse Device Effect (ADE): an adverse event related to the use of the medical device

Serious Adverse Event (SAE / pre-event): an event that results in i) death; ii) life-threatening injury or illness; iii) lasting harm to the body or bodily functions; iv) hospitalization or prolongation of existing hospitalization or required medical or surgical treatment are necessary to prevent i to iv.

Serious Adverse Device Effect (SADE): a serious incident which is related to the use of the medical device.

An almost-event is an equipment incident which does not have a serious output because of intervention before the event has evolved.

Serious incidents and near-incidents caused by improper treatment or error due to technical errors or defects in the equipment, instructions, labelling, use or maintenance of the equipment.

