A summary of product characteristics of the PleurX Peritoneal Catheter listed in the Investigational Brochure will be used as a reference document when it is assessed whether a serious related adverse event is expected or unexpected.

Grading of adverse events:

The investigator should attempt to identify all clinical and objective reactions from subjects and determine their relationship with the use of the allocated intervention (PleurX tunnelated catheter or repeated large volume paracentesis). Reactions, if there are any, should be graded according to the following scale:

1 = slight

2 = moderate

3 = severe

4 = life-threatening

Reporting of side effects of AEs and SAEs/SADEs

The investigator is responsible for ensuring that all adverse events are recorded in the patient's Case Report Form.

The sponsor is responsible for ongoing monitoring of the study's risk/benefit relation. The following must always be always immediately reported to the Danish Medicines Agency: any potential SAEs/SADEs and any situation that may affect the safety of the study subjects or the performance of the study. Similarly, reports should be made to all investigators and the Research Ethics Committees involved.

The sponsor shall at all time be kept informed by the investigator of any adverse events. At the end of the trial, the final report shall contain a description of all side effects.

Serious Adverse Device effect (SADE): Should be reported immediately by the investigator to the sponsor (sponsor-investigator). SADEs must be reported annually by the Investigator to the Research Ethics Committee throughout the whole trial period, together with a report on the safety of the trial subjects.

Fatal or life-threatening SADEs must be reported within 7 days of the sponsor becoming aware of them, and within 8 days of the report the sponsor must inform the Danish Medicines Agency of all relevant information on the follow-up.

All other SADEs should be reported to the same authorities within 15 days of the sponsor (sponsor-investigator) being informed of these.

All reports must be accompanied by comments on any consequences there are for the trial.

The sponsor (sponsor-investigator) will also inform the manufacturers of the medical device.

STATISTICS AND DATA MANAGEMENT

Sample Size Considerations

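### The protocol sets two different causality targets, and its only related-event classes are PleurX-only, so serious harm judged related to paracentesis has no matching class

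*Protocol*

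**What the plan says.** The Objectives section sets a comparative question about harm: "To evaluate the beneficial and harmful effects of the PleurX catheter compared with large volume paracentesis". Adverse events are a secondary outcome, and the outcome list refers to the later safety section for their definition.

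That safety text gives two causality instructions:

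- Adverse Events: "The investigator must assess the relationship between an adverse event and the study medical device using the following guidelines". The section Medical device and labelling settles what this device is: "The medical device tested is the PleurX tunnelated catheter (Pleurx Peritoneal Catheter System".
- Grading of adverse events: the investigator should identify reactions and "determine their relationship with the use of the allocated intervention (PleurX tunnelated catheter or repeated large volume paracentesis").

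Two further sentences in Adverse Events do not settle which target applies. The AE definition covers "any event, sign or symptom occuring during the study whether the AE is considered to be related to the intervention or not". The recording rule is "The type, potential relationship, severity, starts and end date for all AE must be recorded", without saying what the relationship is to.

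The related classes that follow are tied to the device: "Adverse Device Effect (ADE): an adverse event related to the use of the medical device". The serious counterpart, SADE, is defined in the same way.

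For background treatment, the Interventions section states: "Both interventions (PleurX catheter and large volume paracentesis) will be combined with albumin and the antibiotic ciproxin 500 mg once daily".

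**The concern.** Investigators assign relatedness when the event happens. If the form and the training follow the device instruction, the question has no meaningful answer for a control patient who carries no PleurX catheter. If they follow the grading instruction, it has an answer in both arms, but the protocol offers a named class for that answer only when PleurX is the cause. Sites could reasonably read the two sections differently.

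At stake is the attribution of harm in a trial whose objective is to compare harms. Safety tables tend to be built from the classes a protocol defines, and here those classes can be filled from one arm only. An analysis plan cannot reliably repair this later, because a causality judgement that was never asked for, or was asked against the wrong target, cannot be rebuilt from the data.

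**Working it through.** No arithmetic applies. The check is to set each safety rule beside the target it uses.

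| Rule | Protocol section | Target |
| --- | --- | --- |
| Causality, worded as *must* | Adverse Events | Study medical device, i.e. PleurX |
| Causality, worded as *should* | Grading of adverse events | Allocated intervention, PleurX or paracentesis |
| AE definition | Adverse Events | The intervention; counted whether related or not |
| Relationship recorded for every AE | Adverse Events | Not stated |
| ADE and SADE | Adverse Events | Device only |
| Expectedness of serious related events | Text just before Grading of adverse events | PleurX product summary only |
| 7-day and 15-day deadlines | Reporting of side effects | SADEs only |
| Immediate report to the authority | Reporting of side effects | Any potential SAE or SADE, either arm |

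**Step 1: are the two causality targets the same?** No. In the PleurX arm they overlap for events caused by the catheter. In the control arm the first asks about a device the patient normally does not have, and the second asks about paracentesis.

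**Step 2: where does each answer go?** Take bowel perforation, which Potential Risks names for both interventions. At PleurX insertion it is a serious event related to the device, hence a SADE, with a reference document for expectedness. At a control paracentesis it is an SAE. Under the grading section it can be judged related to paracentesis, but no related-serious class carries that judgement and no reference document is named for its expectedness.

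**Step 3: what would a table by ADE/SADE show?** With 16 patients planned per arm, and assuming no control patient receives a PleurX catheter, the 16 controls contribute no ADE or SADE by definition, whatever happens at their paracenteses. Potential Risks assumes a combined risk of 10% for the listed procedural events in both groups. The defined classes therefore cannot display the equality that the protocol itself assumes.

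**Step 4: the common treatments.** No section asks whether an event is related to albumin or ciproxin. Taking the Interventions section at face value, both arms are assigned both, so this omission weakens attribution without by itself favouring an arm.

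**The case against.** The strongest reply is that the protocol already requires what is needed. The grading section asks for relatedness to paracentesis by name. The AE definition does not depend on relatedness, a relationship must be recorded for every AE, and every potential SAE in either arm goes immediately to the authority. ADE and SADE are device terms, natural in a protocol run under a device good-practice standard. The CRF is not shown and may hold a suitable field. How safety tables are built is commonly left to an analysis plan.

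Most of this stands, and it rules out several stronger readings that a reader might infer:

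- *That paracentesis harm can never count as treatment-related.* The grading section contradicts this. What is missing is a matching class, not any route to the judgement.
- *That related harms will come out as 1.6 against 0.* A reader might take 16 × 0.10 = 1.6 expected cases per arm and set the controls to zero. That ignores the grading instruction and presumes an ADE/SADE comparison that neither the outcome list nor Statistical analyses announces.
- *That serious control-arm complications escape reporting.* The 7-day and 15-day limits are written for SADEs, but the immediate-reporting rule covers SAEs in both arms. Extending the dated limits to controls is not needed on this ground.
- *That the silence on ciproxin biases the comparison.* Both arms are assigned it.

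The reply does not remove the conflict between the two causality instructions. Nor does it supply a related-serious class or an expectedness reference for the control procedure. A possible CRF field does not settle which instruction the investigator must follow.

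**Conclusion.** The point holds as an inconsistency with a structural consequence. The protocol names two causality targets, and its related classes and expectedness reference serve only one of them. A serious event judged related to paracentesis stays an SAE without a matching related class, and any between-arm tabulation by ADE/SADE would be one-sided by construction.

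No numerical size can be given. The asymmetry is complete for the ADE/SADE labels and absent from a count of all AEs or SAEs so far as causality classes are concerned. Under the grading section's assessment it depends on how sites apply the conflicting instructions. The conclusion assumes that control patients are not given a PleurX catheter. Treating the albumin and ciproxin gap as minor assumes that both arms receive these treatments as the Interventions section states.

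The change should be made, because the objective is comparative harm and causality is fixed at the time of the event.

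**What to change.** Reconcile the Adverse Events and Grading of adverse events sections into one causality item, worded and completed identically in both arms, with these answers:

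1. related to the allocated drainage procedure or device;
2. related to protocol-mandated albumin or ciproxin;
3. related to underlying disease or another cause.

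Keep ADE and SADE as the device subset for regulatory reporting only. State that the between-arm safety comparison rests on all AEs and SAEs, and on procedure-related events defined the same way in each arm, and that ADE/SADE counts are not used to compare the arms.

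The cost is revised protocol wording and one CRF item.

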The primary outcome measure is paracentesis free survival. With an estimated probability of paracentesis free survival set to 0.3 at the end of the trial, an allocation ratio of 1:1, alpha 5% and power 80%, the required sample size is estimated to be a total of 28 patients (14 patients in each group). After taking into account the risk of participant dropout the sample size is set to be 32 patients (16 patients in each group).

Statistical analyses

We plan to include all patients randomised (intention to treat) regardless of compliance or follow up. Patient characteristics will be summarised using medians with interquartile range or proportions. Groups will be compared using t-tests or chi-square tests as appropriate. The level of significance will be set to 5%. The primary outcome measure will be evaluated using Kaplan Meier Plots and log-rank tests. Univariate and multivariate logistic regression analysis will be conducted to identify potential predictors of paracentesis free survival.

Handling of data

Data will be retrieved from medical records, information provided by the patients at trial visits as well as laboratory (biochemistry) assessments and investigational results. Data will be collected to Case report forms and entered into an electronic database by the principal investigator. Case report forms from the supporting sites will be sent by secure mail to the principal investigator. The database is anonymous. A trial participant identification list will be stored safely by the principal investigator.

Missing data

During the trial, we plan to search for information about missing data in the medical records. Investigators will pursue the options of repeating biochemistry and blood analyses when this is possible. Invasive procedures will not be repeated, should data be missing after the participant has completed the trial investigations.

Quality Control

The study personnel will be trained and tested in all study related procedures to ensure adequate quality control. In particular, investigators will be tested 0to ensure the optimal use of the interventions assessed (PleurX and large volume paracentesis). All investigators are specialised hepatologists with extensive experience in the management and observation of patients with refractory ascites including experience in the use of the PleurX and large volume paracentesis through their clinical work.

Data registration and rules for the control of investigation procedures

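### Logistic regression for predictors of paracentesis-free survival discards the event times and would rest on about five paracentesis-free patients; an exploratory Cox model suits the outcome better

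*Protocol*

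**What the plan says.** The Sample Size Considerations section of the protocol states: "The primary outcome measure is paracentesis free survival". The one rate it supplies reads: "With an estimated probability of paracentesis free survival set to 0.3 at the end of the trial". It does not say which arm this describes and gives no comparator rate or hazard ratio. The size is 28, raised to 32 (16 per arm) for dropout.

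The Statistical analyses section includes all randomised patients and evaluates the primary outcome with Kaplan-Meier plots and log-rank tests. The next sentence is: "Univariate and multivariate logistic regression analysis will be conducted to identify potential predictors of paracentesis free survival". It gives no covariate list, no statement on whether allocation is a covariate, no time point, and no rule for a patient whose follow-up ends early.

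Two other places bear on the numbers. Under Ethical considerations, every participant is described as needing repeated paracentesis, at intervals given as weekly, monthly or bimonthly. Under Adverse Events the protocol says: "The median survival for patients with cirrhosis and diuretic resistant ascites is six months". The synopsis sets follow-up at six months.

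**The concern.** Two adjacent sentences treat one outcome in two ways: first as a time to event, then as a yes/no status. The second treatment discards the event times and requires every patient to be classified at six months. Control patients are treated by paracentesis itself, so few or none should reach six months without one. The smaller outcome class, which limits what a logistic model can estimate, may therefore be a handful of patients almost all in one arm. At stake is whether the predictor analysis can produce interpretable estimates. The test of the primary outcome is not at stake.

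**Working it through.** **The plan's own figure.** The 28 cannot be recomputed, because only one rate is given. With two-sided 5% alpha and 80% power, incompatible assumptions return it: 0.3 v 0.02 by log-rank (Schoenfeld), or 0.3 v 0.82 by comparing two proportions. The sample size therefore does not settle which arm 0.3 describes. I take it as the PleurX rate, as an assumption, for the reason in step 1, and show the other reading in step 6.

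**1. Control rate.** Assume paracenteses occur at random at rate λ per month, independently of death, and that half of the patients are alive at six months (the stated median survival). Then P(alive and paracentesis-free at six months) = 0.5 × exp(-6λ). Bimonthly can mean twice a month or every two months, so both are shown.

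| Need | λ | P(alive, no paracentesis) | P(0 of 16 controls) |
|---|---|---|---|
| Twice a month | 2 | 0.5 × e^-12 = 0.000003 | 100% |
| Monthly | 1 | 0.5 × e^-6 = 0.0012 | 98% |
| Every two months | 0.5 | 0.5 × e^-3 = 0.025 | 67% |

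Weekly need gives a value that is effectively zero.

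**2. Size of the outcome classes.** Paracentesis-free: 16 × 0.3 = 4.8 in PleurX and about 0 in controls, so about 5 of 32. Events: 16 × 0.7 + 16 = 27.2, so about 27.

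**3. Allocation in the model.** If no control is paracentesis-free, allocation separates the outcome and the maximum-likelihood odds ratio is not finite. The exact chance of an empty control cell is (1 - p)^16: 100% at p = 0, 0.99^16 = 85% at 0.01, 0.95^16 = 44% at 0.05, 0.90^16 = 18.5% at 0.10. Simulated trials (400 per setting, PleurX rate 0.3, none to four unrelated covariates beside allocation, separation checked by linear programming) gave 100%, 81-86%, 40-46% and 18-23%.

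Example, 0/16 v 5/16: the ordinary logistic fit did not converge (log odds ratio about 24, standard error about 50,000). Adding 0.5 to each cell, which is equivalent to the Firth penalty here, gives (5.5 × 16.5)/(0.5 × 11.5) = 15.8. The standard error of its log is √(1/5.5 + 1/16.5 + 1/11.5 + 1/0.5) = 1.53, and the approximate 95% interval is 0.8 to 314.

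**4. Allocation left out.** With one to four unrelated covariates, separation occurred in only 0-6.5% of simulated trials. Such a model usually fits, but with three covariates it has 4.8/3 = 1.6 paracentesis-free patients per coefficient. It also omits the factor expected to matter most.

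**5. Six-month status.** The dropout allowance is 32 - 28 = 4 patients, about as many as the 4.8 expected to be paracentesis-free. How patients with incomplete follow-up are classified could therefore change the result materially.

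**6. The other reading.** If 0.3 were the control rate and 0.82 the PleurX rate, about 16 × 0.3 + 16 × 0.82 = 17.9 patients would be paracentesis-free and 14.1 would have events. The chance of any empty cell would be about 4.5%. Separation would no longer be a practical concern, but the loss of event times would remain. This reading sits badly with the Ethical considerations section.

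**The case against.** The regression is a secondary search for predictors, and logistic regression at a fixed horizon is not invalid in kind. Deaths do not censor a paracentesis-free survival outcome, because death is itself an event. Follow-up is a fixed six months, and the Subject Withdrawal section seeks outcomes of withdrawn patients from records. Six-month status should thus be known for most patients. All of this stands. It limits the status problem to patients who leave without traceable records, and it makes this a comment on a secondary analysis. It does not restore the lost event times or enlarge a class of about five.

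A reader might infer that the model will certainly fail. The protocol does not support that: it does not say that allocation is a covariate, it does not name the arm for 0.3, and at a control rate of 0.05 separation is closer to an even chance.

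A reader might also infer that t-tests are planned for paracentesis counts and quality of life, and chi-square tests for sparse adverse events, from the sentence "Groups will be compared using t-tests or chi-square tests as appropriate". That sentence follows the description of patient characteristics, names no outcome and leaves the choice open. The methods for those outcomes may be in an analysis plan that is not shown. Moreover, a t-test on counts would be biased as a comparison of paracentesis rates only if mortality differed between arms. In simulation with equal rates and equal mortality its type I error was 5.1%.

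**Conclusion.** The point holds for the logistic regression only. The stated method does not suit an outcome that the same section treats as time-to-event. If 0.3 is the PleurX rate and the control rate is near zero, the model rests on about 5 paracentesis-free patients, against about 27 events for a time-to-event model. A model that includes allocation would probably have no finite odds ratio for control rates from 0 to 0.01, with a 40-46% chance of this at 0.05. A model without allocation would usually fit but could not support several covariates. If 0.3 is the control rate, the sparseness largely disappears and the mismatch of method remains. A reader should not infer that the primary result is compromised, because the log-rank analysis does not depend on this regression.

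**What to change.** Replace the logistic regression with Cox regression for paracentesis-free survival. Include allocation plus at most one or two covariates named in advance, apply a Firth penalty if the estimate is unstable, and label the analysis exploratory. With about 27 events and three coefficients, this gives 27/3 = 9 events per coefficient, against 4.8/3 = 1.6 for the logistic model. State which arm the 0.3 describes, so that the expected number of events can be checked.

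The cost is a change of wording. The Kaplan-Meier analysis already needs event and censoring times, so no new data are required. The downsides are that fewer predictors can be examined jointly and that proportional hazards must be assumed. That assumption deserves a check, since control events are likely to cluster early.
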